## Abstract

**Introduction:**

About 2.3% of the adult population in Sweden are considered to suffer from problem gambling, and it is estimated that only 5% of those seek treatment. Problem gambling can have devastating effects on the economy, health and relationship, both for the individual who gambles and their concerned significant other (CSO). No empirically supported treatment exists for the CSOs of people with problem gambling. Consequently, the aim of this study is to develop and evaluate a programme aimed at CSOs of treatment-refusing problem gamblers. The programme will be based on principles from cognitive behavioural therapy (CBT) and motivational interviewing. To benefit as many CSOs as possible, the programme will be delivered via the internet with therapist support via encrypted email and short weekly conversations via telephone.

**Methods and analysis:**

This will be a randomised wait-list controlled internet-delivered treatment trial. A CBT programme for the CSOs of people with problem gambling will be developed and evaluated. The participants will work through nine modules over 10 weeks in a secure online environment, and receive support via secure emails and over the telephone. A total of 150 CSOs over 18 years of age will be included. Measures will be taken at baseline and at 3, 6 and 12 months. Primary outcomes concern gambling-related harm. Secondary outcomes include the treatment entry of the individual who gambles, the CSO's levels of depression, anxiety, as well as relationship satisfaction and quality of life.

**Ethics and dissemination:**

The protocol has been approved by the regional ethics board of Stockholm, Sweden. This study will add to the body of knowledge on how to protect CSOs from gambling-related harm, and how to motivate treatment-refusing individuals to seek professional help for problem gambling.

**Trial registration number:**

NCT02250586.

## Introduction

An estimated 70% of the Swedish population aged 16–84 years participate in gambling.^1^ Most experience no negative consequences, but for a small group of people gambling is problematic. The most recent national survey estimated that around 2.3%^1^ of the adult population suffer from problem gambling. Consequently, their gambling behaviour can have devastating effects on both their own and their concerned significant others’ (CSOs’) economic status, health and relationships. A large proportion (18%) of the adult Swedish population see themselves as CSOs of people with problem gambling.^2^ Moreover, the Swedish National Institute of Public Health has estimated that approximately 260 000 (∼3%) individuals cohabitate with an individual who gambles problematically, and among them 76 000 are children.^1^

The effects of problem gambling on the CSOs have been well documented in the literature.^3–6^ Problem gambling causes enormous financial problems for the affected family, such as debts, losses of property, loans that are overdue, maxed credit cards and being chased by creditors.^7^ As a result of these consequences, some CSOs report feeling depressed, a low quality of life and some even attempt suicide.^8^
^9^ Other CSOs experience considerable anger and anxiety as a result of problem gambling.^4^
^10^ CSOs also report several stress-related problems, for example, headaches, bowel problems and sleep disturbances.^11^
^12^ The CSO's relation to the individual who gambles can also be severely affected, and many CSOs report escalating conflicts in the home, dissipation of trust and disturbed relationships with family and friends.^3^
^4^
^9^
^13^ In a representative sample in Norway, Wenzel *et al*^14^ found that 63% of the CSOs reported that problem gambling had worsened the family's financial situation, and 65% reported that it had led to conflicts in the family. Many CSOs report that they are often left feeling isolated and unsupported.^15^

In Sweden, it has been estimated that only about 5% of the people with problem gambling seek professional help.^1^ Numerous researchers have suggested that CSOs can play a key role in getting these people with problem gambling to enter treatment, and they have highlighted the need to better equip CSOs to cope with problem gambling.^7^
^13^
^16–23^ Even though financial concerns are often the main reason that gamblers seek help,^24^ many individuals with a gambling problem report concerns for CSOs as an important reason for entering treatment.^18^
^25^ Additionally, as many as 50% of people with problem gambling report that they rely on informal help provided by their CSO to overcome their gambling problem.^16^

Research on support programmes aimed at CSOs of people suffering from addiction has shown promising results in getting the treatment-refusing individual into treatment. The approach with the strongest empirical support is the *community reinforcement and family training (CRAFT)*.^26–28^ The CRAFT approach has been modified and tested with CSOs of people with problem gambling in two studies.^20^
^29^ Both studies used a self-help workbook to deliver the training, and found that the programme had a significant effect on the number of days gambling, CSOs’ programme satisfaction and experiences of having their needs met. However, no differences were found between the CRAFT approach and the control group on rates of treatment engagement.

Few studies have evaluated interventions that focus on working with CSOs of people with problem gambling in their own right. In 2006, Rychtarik and McGillicuddy performed a preliminary evaluation of a coping skills training programme, aimed at CSOs with a partner that gambled problematically. They found a large reduction in symptoms of depression and anxiety in the coping skills training group relative to a wait-list control. However, they found no differences between groups on partner gambling or treatment entry. These findings should be considered highly preliminary since the study involved just 23 participants.

In 2013, The Swedish National Helpline received 600 calls (31% of total) from CSOs.^31^ Research has shown that most CSOs typically turn to self-help, online or telephone support before seeking professional help.^18^ Rodda *et al*^32^ looked at reasons why CSOs chose web-based counselling in Australia, and found that ease of access, privacy and anonymity were the main reasons. Another study on the same service^33^ found that the large majority of CSOs accessing web-based counselling reported emotional distress and impacts on relationship, social life and finances due to problem gambling. There is also evidence that shame and stigma are the main barriers for CSOs in seeking help;^18^
^34^
^35^ therefore, it is possible that an internet-delivered treatment could seem attractive to these CSOs. Cognitive behavioural therapy (CBT) has been readily adapted and evaluated over the internet. These internet-delivered CBT interventions have often achieved treatment effects that are comparable to face-to-face therapy in several studies.^36–38^ Moreover, internet-delivered CBT has also been efficaciously implemented with problem gamblers.^39^

### Aims and hypotheses

Earlier studies have found limited success in helping CSOs deal with problem gambling. Protecting the CSO from gambling-related harm can be achieved partly by motivating the individual who gambles to enter treatment, thus hopefully ending problem gambling, and partly by focusing on the CSO’s needs in their own right. Since the available support for CSOs is scarce in Sweden, the aim of this study is to develop and evaluate an internet-delivered CBT programme for CSOs of people with problem gambling. The programme will be inspired by CRAFT but can rightfully be seen as a CBT programme—utilising standard CBT techniques. Thus, this programme is referred to as CBT for CSOs of people with problem gambling (CBT-CSO).

The aim of this study will be to investigate the effects and feasibility of an internet-delivered CBT-CSO programme on (1) gambling-related harm both for the CSO and the individual who gambles, (2) treatment-seeking rate among the people with problem gambling, and (3) relationship functioning and mental health of the CSOs. It is hypothesised that: (1) the CBT-CSO programme will lead to a reduction in gambling-related harm, and a greater treatment-seeking rate, (2) the CBT-CSO programme will reduce the CSO's anxiety and depressive feelings, (3) the CBT-CSO programme will decrease the amount of time and money spent on gambling by the individual who gambles, (4) the CBT-CSO programme will increase the CSO's relationship satisfaction with the individual with problem gambling.

The programme will be compared to a wait-list control condition. This choice of comparator is justified, since not much is known about the efficacy and feasibility of these types of programmes in this population.

## Methodology

The study will be a randomised controlled trial with two arms: (1) the CBT-CSO programme and (2) a wait-list control. The wait-list group will be offered the CBT-CSO programme after 10 weeks.

### Study population and recruitment

Participants will be recruited nationwide through the Swedish National Gambling Helpline and via media and internet advertisements. Advertisements will be publicised nationwide to the general population in newspapers and on Facebook. Targeted advertisements will be published via Google Adwords. Volunteers will sign up to the study via a public website. After signing up, they will be invited to answer a survey of screening questions and the baseline assessment. If they are eligible, they will be invited to a short telephone interview with one of the study's counsellors. During this interview, the volunteers are informed about the study and get the chance to ask questions. If they agree to participate in the study, they are asked to send in written informed consent via mail. After the consent is received, treatment allocation is performed, and the participant is contacted within the treatment platform.

#### Eligibility criteria

For brevity, we will refer to the participant's related party which gambles as the identified patient (IP).

*Inclusion*: (1) The CSO and the IP are at least 18 years old, (2) the CSO is a parent, child, sibling, friend or partner of the IP. (3) The CSO must have had a relationship with the IP for at least 3 months. (4) Neither the CSO nor the IP has had any treatment in the past 3 months (ie, related to gambling). (5) The IP is currently refusing to start treatment for gambling problems. (6) The CSO is able to read and answer questions in Swedish, and is willing to have phone contact with a counsellor each week. (7) The IP is rated by the CSO as having gambling problems (score 8 or greater) on the Problem Gambling Severity Index (PGSI).^40^ (7) CSOs on psychotropic medication must have been on a stable dose for at least 3 months. *Exclusion*: (1) Presence of a current psychotic or bipolar disorder in the CSO or IP. (2) CSO meets PGSI criteria (8 or greater) for ongoing problem gambling.

### Counsellors

The study's counsellors will be at least a master's level clinical psychology students on their last semester, or experienced staff from the National Helpline who are trained in motivational interviewing (MI).^41^ They will assist the CSOs via encrypted emails and scheduled weekly telephone calls. The length of the calls will be a maximum of 15 minutes per week. The purpose of these calls is to provide positive feedback and answer questions that the CSO might have regarding the content of the modules. In addition to the telephone calls, the counsellors also provide written feedback once a week. They will also send short messages to reinforce the participants’ efforts. The amount of time spent on sending emails is limited to 15 min per week. The counsellors will also try to contact participants who are not responsive both via email and telephone, to see that there are no technical difficulties or other problems. The counsellors will receive training in the study manual and weekly supervision by an experienced CBT therapist.^42^

### Blinding

Neither participants nor counsellors will be blinded to treatment allocation. Baseline assessment occurs prior to randomisation, and follow-up assessment will be self-reported via the internet.

### Trial arms

#### CBT-CSO

The CBT-CSO programme will be based on concepts from CBT, integrative behavioural couples therapy (IBCT)^43^ and MI.^44^ CBT-CSO will be similar to the CRAFT approach in many ways, since both approaches utilise generic CBT techniques, such as psychoeducation, functional analysis and positive reinforcement. Both methods are also targeted specifically at CSOs alone, where the person with the drinking or gambling problem does not participate in the treatment. However, CRAFT was not developed with problem gambling in mind, and it relies heavily on the CSO being able to tell when a person is intoxicated. Gambling can be done anywhere and at anytime and is easy to hide. Therefore, reinforcing intermittent abstinence from gambling is often very difficult. Consequently, our approach will focus less on the CSO being able to tell when the IP has gambled and more on creating an environment that encourages gambling-free activities. The aim is for the CSO and IP to engage in naturally reinforcing activities alone and together, thus hopefully reconnecting with each other and reintroducing non-gambling related reinforcers to the IP. The CSO is also introduced to concepts from MI, such as ‘the stages of change’, ‘asking for permission’ and the concept of ‘resistance’. The purpose is to help the CSO find situations where the IP is more open to change, instead of inadvertently creating resistance. Concrete examples are given of different ways to avoid resistance, and how to lead the conversation forward. Concepts from IBCT are also integrated into the programme. For instance, ‘contingency based change’ is one of the purposes of trying to get the CSO and IP to engage in more activities together, that is, reinforcement from spontaneous positive behaviours. IBCT's concept of ‘acceptance’ is also introduced to help the CSO to better understand the IP's learning history and therefore better cope with the situation. There are also several concepts and exercises that focus on CSOs in their own right. The rationale is that problem gambling has led to the CSOs losing important positive reinforcers in their lives. Therefore, there are reoccurring exercises to engage the CSO in reinforcing activities. The CSOs are prompted to schedule and log these activities. A short summary of the individual modules is provided in table 1.

**Table 1 BMJOPEN2015008724TB1:** Programme contents

Module	Summary content
1. Psychoeducation about gambling problems	Information about the programme and technical platform Gambling problems in general, signs of gambling, and the biopsychosocial model Goals, and how the gambling problem started
2. Functional analysis and gambling free activities	Functional analysis with exercises Gambling urges Alternatives to gambling Reinforcing non-gambling behaviour
3. Rewards and behavioural activation for both the CSO and problem gambler	Helping CSOs reconnect with their values Behavioural activation and rewarding themselves Strategies that make the CSO feel worse Reconnecting with the gambler; doing things together
4. Psychoeducation about motivation and protecting the CSO’s economy	CSO's motivation to support the IP Motivation and gambling; ‘stages of change’ How to talk about gambling and avoiding resistance; ‘asking for permission’ Protecting the CSO's economy Lending money and enabling
5. Common behaviours that inadvertently enable gambling	Enabling Natural negative consequences
6. Communication training and principles from MI	Rolling with the punches Effective communication; ‘soft disclosures’ Active listening and reflections
7. Problem-solving	Problem-solving with exercises Interactive log to perform the steps in problem-solving
8. Inviting the gambler into treatment	Identifying when motivation is high Different treatment options Examples of how to use communication skills Support during treatment Relapses
9. Repetition and evaluation	Repetition, evaluation, and creating an action plan

CSO, concerned significant other; IP, identified patient; MI, motivational interviewing.

The programme will be given as guided self-help with guidance given via a secure email system and telephone. There are nine modules, all of which contain homework exercises and about 5–10 pages of text. Every week a new module is made available to the participant, regardless of whether the previous module has been completed. At the start of the study, the participant is informed that the counsellor will be aiding them for a maximum of 10 weeks. After these 10 weeks, the participant will still have access to the modules but not the counsellor.

All CSOs will receive help from their counsellor in locating professional gambling treatment as close to their home as possible. The National Gambling Helpline has a registry of available treatment options in Sweden, which is regularly kept up to date. In parallel to this study, we are also running a trial on internet CBT for people with problem gambling. The CSO's IP who wishes to enter treatment will be offered the programme used in the parallel study.

#### Wait-list condition

The participants allocated to the control condition will be put on a waiting list and offered the treatment after 10 weeks. The participants will know that they have been randomised to the control group. During these 10 weeks, they will participate in the weekly assessments. The CSOs will receive information about available treatment options—in their area and web-based—for problem gambling.

### Outcome measures and data collection

See table 2 for a list of measures and when they will be collected. All outcomes will be self-reported via the internet. The primary outcome concerns gambling behaviour and consequences for the IP and their CSO. This will be measured by the Inventory of Consequences Scale for the Gambler and CSO (ICS).^45^ The scale was adopted from the substance abuse field and consists of three subscales: (1) consequences for the gambler, (2) negative emotional consequences for the CSO and (3) negative behavioural consequences for the CSO. It was used in a similar study with CSOs of people who gamble.^20^ Internal consistency was good, ranging from α=0.86 to 0.89 for the different subdomains. Test-retest reliability was excellent over 7 to 10 days (ICC=0.93 for all domains).^45^ Although lacking an extensive psychometric evaluation, these results indicate good psychometric properties in a relevant sample. Gambling behaviour will be reported by the CSO, and will be measured by the timeline followback method for the past 30 days, and continuously during the study. CSOs will be asked to report days gambling and money spent. Previous studies have found fair agreement between reports from CSOs and the IP,^45^ indicating that the CSO's report of gambling behaviour is reasonably valid and reliable as a proxy measure of problem gambling behaviour. CSOs will also be asked to report whether and when the IP decided to enter treatment. Treatment engagement is defined as completing at least one treatment session or agreeing to call the National Gambling Helpline. We choose to include calls to the Helpline since they work with MI, and research has shown that such brief interventions can reduce gambling problems.^46^

**Table 2 BMJOPEN2015008724TB2:** Outcomes and their placement during the study

Outcome	Measure	Pretest	Weekly during treatment*	Post-test, 6, 12 months
Primary outcome				
Gambling consequences	ICS	X	X	X
Secondary outcomes				
Treatment engagement	–	X	X	X
Gambling behaviour	TLFB: days, money	X	X	X
Depression	PHQ-9	X	X	X
Anxiety	GAD-7	X	X	X
Relationship	RAS	X	X	X
Quality of life	WHOQOL-Bref	X		X

*Not all measures are answered by all participants every week; see the section about ‘planned missingness design’.

GAD-7, Generalised Anxiety Disorder Scale;^48^ ICS, Inventory of Consequences Scale for the Gambler and CSO;^45^ PHQ-9, Patient Health Questionnaire-9;^47^ RAS, Relationship Assessment Scale;^52^ TLFB, Timeline followback method;^68^ WHOQOL-Bref, WHO Quality of Life Questionnaire-BREF.^53^

PHQ-9^47^ and GAD-7^48^ will be used to measure symptoms of depression and anxiety. PHQ-9 contains nine items, and scored 0–3 with a total score between 0 and 27.^49^ GAD-7 is frequently used to assess general anxiety, and contains seven items (scored 0–3). Both PHQ-9 and GAD-7 are well-established measures with demonstrated good validity and reliability even when administered via the internet.^49–51^ Relationship satisfaction will be measured by the generic version of the Relationship Assessment Scale (RAS).^52^ RAS consists of seven items and has shown good psychometric properties with CSOs of problem gamblers.^45^ The short version of the WHO Quality of Life Questionnaire will be used to measure the CSO’s quality of life; it consists of 26 items and has demonstrated good reliability and validity.^53^

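### Treatment engagement is met by agreeing to call the Helpline, although the stated rationale supports only calls that take place; an unfulfilled agreement would count as treatment entry

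*Protocol article*

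**What the plan says.** The definition is in the protocol article under Outcome measures and data collection: "Treatment engagement is defined as completing at least one treatment session or agreeing to call the National Gambling Helpline". The sentence after it gives the reason: "We choose to include calls to the Helpline since they work with MI, and research has shown that such brief interventions can reduce gambling problems". The sentence before it describes what is collected: "CSOs will also be asked to report whether and when the IP decided to enter treatment". Table 2 shows a dash where the measure for treatment engagement would stand.

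Elsewhere the outcome is called treatment entry. The abstract has "Secondary outcomes include the treatment entry of the individual who gambles". Statistical analyses plans discrete-time event history models of whether and when entry occurs, and joint modelling of engagement with the ICS. Sample size gives the outcome its own power statement: 15% on the wait-list against 35% with CBT-CSO, 75 per group, 80% power. Treatment entry is not defined separately anywhere.

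On reporting, the article states "All outcomes will be self-reported via the internet" and, under Blinding, "Neither participants nor counsellors will be blinded to treatment allocation".

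**The concern.** The text describes three different events. The definition counts a completed session or an agreement to call. The rationale concerns calls. The description of data collection concerns the moment at which the gambler (the IP) made a decision. Only a session or an actual call brings the IP into contact with treatment, and only these match the name treatment entry.

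Read literally, an IP who says yes and never calls is an event, possibly dated by that conversation. Module 8 in Table 1 teaches CBT-CSO participants how to raise treatment with the IP, whereas wait-list participants receive information on treatment options. More unfulfilled agreements in the CBT-CSO arm are therefore plausible, and would widen the recorded difference without any difference in treatment contact. If they are equally frequent in both arms, they shrink a true difference and cost power. In both cases the survival analysis and the joint model mix intention with behaviour.

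**Working it through.** **Inputs from the protocol article (Sample size; Randomization).** Entry 15% (wait-list) and 35% (CBT-CSO), 75 per arm, 1:1, α = 0.05. Sidedness is not stated; two-sided is assumed.

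**Inputs assumed.** The rate f of agreement without a call among IPs who do not enter treatment. The document gives no value, so a range is used.

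**Formulas.** Recorded rate = p + (1 − p) × f, where p is the true entry rate. Power for two proportions, normal approximation with pooled variance under the null:

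Φ{ [ |p₂ − p₁|√n − 1.96 √(2p̄(1 − p̄)) ] / √(p₁(1 − p₁) + p₂(1 − p₂)) }, with p̄ = (p₁ + p₂)/2.

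**Step 1: the plan's own figure.** For 0.15 vs 0.35, p̄ = 0.25. The numerator is 0.20 × 8.660 − 1.96 × 0.6124 = 1.732 − 1.200 = 0.532. The denominator is √(0.1275 + 0.2275) = 0.596. Φ(0.893) = 81.4%, and 73 per arm are needed for 80%. The stated 80% with 75 per group reproduces, so the power arithmetic is not at issue.

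**Step 2: no true difference, unequal unfulfilled agreement.** True entry is 15% in both arms.

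| f control | f CBT-CSO | Recorded control | Recorded CBT-CSO | Chance of p < 0.05 |
|---|---|---|---|---|
| 0% | 5% | 15.0% | 0.15 + 0.85 × 0.05 = 19.3% | 10% |
| 0% | 10% | 15.0% | 0.15 + 0.85 × 0.10 = 23.5% | 26% |
| 5% | 20% | 19.3% | 0.15 + 0.85 × 0.20 = 32.0% | 43% |
| 0% | 23.5% | 15.0% | 0.15 + 0.85 × 0.235 = 35.0% | 81% |

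The last row marks the limit: it is the rate at which unfulfilled agreement alone would reproduce the whole planned effect. It is not a forecast.

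**Step 3: true difference as planned, equal unfulfilled agreement.** True entry is 15% vs 35%. The recorded difference is 0.20 × (1 − f).

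| f in both arms | Recorded rates | Power at 75 per arm | n per arm for 80% |
|---|---|---|---|
| 0% | 15.0% vs 35.0% | 81% | 73 |
| 5% | 19.3% vs 38.3% | 73% | 88 |
| 10% | 23.5% vs 41.5% | 66% | 106 |
| 20% | 32.0% vs 48.0% | 52% | 146 |

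**The case against.** The strongest reply is that agreement to call may be loose drafting. The authors describe their own choice as "We choose to include calls to the Helpline since they work with MI", so actual calls may have been meant. That is possible, but the definition is the operative sentence and it says otherwise; the reply is itself a reason to correct it.

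A second reply is that agreement has meaning here. Every IP is declining treatment at entry, and Aims and hypotheses speaks of treatment-seeking, so a move from refusal to agreement is a step. This stands in part and is why agreement deserves to be reported. It does not make agreement the same as treatment entry, which is what the abstract and the analysis and sample-size sections name.

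Several stronger readings are tempting but not supported:

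- **That unfulfilled agreements will gather mainly in the CBT-CSO arm.** This is plausible but not shown. Module 8 is released late in a ten-week programme, although earlier modules also cover communication, and no rates are given for either arm.
- **That 43% is a type I error rate.** If more IPs really do agree in one arm, the null hypothesis for the outcome as defined is false. The fault lies in interpreting the result as treatment entry.
- **That the questionnaire itself uses a third definition.** The item is not shown; the article only describes it in prose.
- **That unblinded reporting is the core of the problem.** Participants know their allocation (for controls, "The participants will know that they have been randomised to the control group"), but this applies to every outcome in the trial and is not specific to this definition.

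**Conclusion.** The point holds as a conflict between a stated definition and its own rationale, in a secondary outcome that has its own power statement and enters the joint model. As written, the rule can record entry where no treatment contact took place.

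The direction and size of the effect cannot be taken from the document. Over the milder assumed rates in Step 2, the chance of a significant recorded difference with no true difference in entry runs from about 10% to 43%. Under equal unfulfilled agreement of 5% to 20%, power drops from 81% to between 73% and 52%. These figures rest on the assumed rates, two-sided testing and a simple comparison of proportions, which the article treats as essentially equivalent in power to the survival analysis.

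The primary ICS comparison is not affected. The session component already requires completion, so only the Helpline component needs repair. The correction should be made, but it does not put the trial's main conclusion at risk.

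**What to change.** Define the event as a completed Helpline call or a completed first treatment session, whichever comes first, and date it by that contact. Ask the CSO for that date. Use this event in the survival analysis and in the joint model with the ICS. Report agreement to call, or a decision to enter treatment, separately as an exploratory outcome.

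The cost is one sentence in the outcome definition and a matching question to the CSO. The downside is somewhat fewer events. The change closes the gap between intention and behaviour. It does not remove bias from reporting by CSOs who know their allocation, since the same person still supplies the date.
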